### Sample size

The sample calculation considered two independent samples with an estimated proportion of the ulcer healing rate of 75% for group 1, which will be treated with cell therapy, and 30% for group 2, which will be treated with hydrogel dressing. Assuming a test power of 80% and a significance level of 5% for a two-sided test, the sample was defined as 20 participants for group 1 and 20 participants for group 2 (1:1 allocation). This study was designed to be analyzed with intention to treat (ITT).

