To prevent data loss, we will implement the measures previously outlined. However, if a category has missing data for 50% or more of the participants, that category will be removed from the analysis. In some cases, where only a portion of the data is missing, the missing data may not be included in the analysis. If more than 10% of the data is missing, we will consider using seasonal adjustment with linear interpolation, especially if the data shows trends and seasonal patterns. For data sets with a significant amount of missing data (while still less than 50%), multiple imputations will be employed.

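### The missing-data rules offer a time-series method that cannot supply a missing final healing status, permit open-ended exclusions that conflict with ITT, and overlap without a boundary

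*Protocol article*

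**What the plan says.** The last paragraph of the protocol article's *Sample size and Statistics* section gives four rules for missing data:

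- Removal: "if a category has missing data for 50% or more of the participants, that category will be removed from the analysis".
- Leaving out: in some cases where part of the data is absent, "the missing data may not be included in the analysis". No threshold or criterion is given.
- Interpolation: "If more than 10% of the data is missing, we will consider using seasonal adjustment with linear interpolation", with particular reference to data that show trends and seasonal patterns.
- Multiple imputation: "For data sets with a significant amount of missing data (while still less than 50%), multiple imputations will be employed". The lower bound is not defined.

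None of the four is specific to the primary outcome. The *Sample size* section fixes the analysis principle: "This study was designed to be analyzed with intention to treat (ITT".

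The primary efficacy outcome (*Primary outcomes*) is total epithelialization of the ulcer together with limb salvage. *Participant timeline* sets reassessments at days 7, 30, 60, 90 and 120, with day 120 as the closing assessment.

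Three other sections determine who can lack a final status. *Data collection plan* treats death and amputation as endpoints, not as data loss. The section on participant withdrawal stops data collection once consent is revoked. The section on suspension of the intervention lists loss to follow-up, clinical worsening and active ulcer infection among the reasons for withdrawal, and then says that participants whose intervention is discontinued will be followed up.

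**The concern.** Seasonal adjustment belongs to long, regularly spaced series with a repeating cycle. This trial has a handful of irregular visits per person and a yes/no primary efficacy outcome read at the end. A method that needs a value on each side of the gap does not help where the final value is the one missing.

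The permission to leave missing data out turns the primary comparison into a complete-case analysis whenever it is used, which is not what the sample-size section promises. Between 10% and 50% missing, interpolation, imputation and omission can all be claimed as the planned approach.

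At stake is the credibility of the primary healing result. With 20 participants per group, the handling of a few missing outcomes can decide whether the result is significant, and the choice would be made with the data in view.

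**Working it through.** **1. The plan's own figure.** The inputs come from the *Sample size* section: "estimated proportion of the ulcer healing rate of 75% for group 1", "30% for group 2, which will be treated with hydrogel dressing", and "Assuming a test power of 80% and a significance level of 5% for a two-sided test". With the pooled-variance formula, p̄ = (0.75 + 0.30)/2 = 0.525:

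n = [1.960·√(2·0.525·0.475) + 0.842·√(0.75·0.25 + 0.30·0.70)]² / 0.45² = 18.1, so 19 per group.

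The stated 20 per group is reproduced closely. At 20 per group, power is 84.1% for the chi-square test and 73.1% for Fisher's exact test. The point does not rest on an error in sample size, but the document states no allowance for dropout.

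**2. Does interpolation fit?**

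- Seasonality: five post-baseline visits, at unequal spacing, over 120 days. No cycle can be seen or estimated.
- Final status: linear interpolation needs an observed value before and after the gap. Nothing is scheduled after day 120, so someone who has left has no later value.
- Scale: between not healed (0) and healed (1), interpolation returns a fraction, which is not a healing status.
- What it could do: fill a missed intermediate visit for a continuous measure, such as ulcer area, when a later value exists. That does not help the primary healing outcome.

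**3. Do the rules have boundaries?**

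| Share missing | Rules that can apply |
|---|---|
| up to 10% | leave out; imputation if judged significant |
| over 10%, under 50% | leave out; interpolation; multiple imputation |
| 50% or more | variable removed |

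In the middle row the text does not say which rule takes precedence.

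**4. What case dropping can do (selected illustrations).** Four missing of 40 is 10%. The interpolation rule starts above 10%, so these examples show omission only.

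| Healed, missing dropped | Fisher p | Same, missing = not healed | Fisher p |
|---|---|---|---|
| 13/17 v 7/19 (3 and 1 missing) | 0.023 | 13/20 v 7/20 | 0.113 |
| 14/18 v 5/18 (2 and 2 missing) | 0.007 | 14/20 v 5/20 | 0.010 |
| 13/18 v 5/18 (2 and 2 missing) | 0.018 | 13/20 v 5/20 | 0.025 |

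The Pearson p-values for the first row are 0.017 and 0.058. The first row crosses 5% under either test; the other two rows do not.

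**5. Direction of bias.** Suppose the true healing rate is 30% and a fraction x of non-healers in one group goes unseen and is dropped. The observed rate is 0.30/(1 − 0.70x): 34.9% for x = 0.2 and 41.7% for x = 0.4.

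**6. Power under two simple rules.** The missing fraction d is assumed equal in both groups and unrelated to outcome. Dropping leaves 20(1 − d) per group at 75% v 30%. Counting missing as not healed keeps 20 per group at 75%(1 − d) v 30%(1 − d). Chi-square power:

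| d | Dropped | Counted as not healed |
|---|---|---|
| 10% | 79.8% (n = 18) | 74.6% (67.5% v 27%) |
| 20% | 74.5% (n = 16) | 64.5% (60% v 24%) |
| 30% | 68.3% (n = 14) | 54.5% (52.5% v 21%) |

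**The case against.** The wording is softer than a quick reading suggests. Interpolation is only to be considered, and omission is only permitted. The two firm rules are multiple imputation for significant missingness below 50% and removal at 50% or more. Multiple imputation can supply a missing healing status, so a reader who infers that the plan as a whole has no means of doing so, or that it prescribes interpolation, goes further than the text. This stands, and it is why the point concerns an unsuitable option and an undefined boundary.

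A reader might also infer that participants with the worst course simply disappear from the analysis. The documents do not support that. Death and amputation count as endpoints. Follow-up is promised after discontinuation, including for active ulcer infection, although the same section also calls these participants withdrawn from the study. The gap that clearly remains is loss to follow-up and revoked consent. For the same reason, loss of the primary safety outcome under the 50% rule is remote; laboratory or perfusion items are the likelier candidates.

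Nor would interpolation give someone who left a smooth course to healing, because without a later value it gives them nothing.

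Finally, the 13/17 v 7/19 example is a chosen one. It shows that a few missing outcomes can decide significance, not that they will.

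**Conclusion.** The point holds in this form. The article itself names a method that does not fit the visit schedule or the binary outcome. It permits omission without a criterion despite an intention-to-treat commitment, and it leaves the choice among omission, interpolation and imputation open until the data are seen. These are stated rules, not detail deferred to an analysis plan.

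The defect in the wording is certain; its effect on the result is not. No dropout rate is given, so every missing fraction above is an assumption. Four missing outcomes split 3 v 1 can move Fisher's p from 0.023 to 0.113, while an even split can leave the conclusion as it was. The reasoning takes day 120 as the final assessment, as in the timeline section; the abstract gives 90 days of monitoring. For a participant who has left, the argument is the same at either day.

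**What to change.** - Delete the seasonal-adjustment and interpolation rule, and the open-ended permission to leave missing data out.
- For the primary healing outcome, analyse all randomised participants in their assigned groups under one rule fixed in advance and applied equally to both groups. The rule could be multiple imputation, which the plan already names, using group, baseline and earlier visits; or missing counted as not healed. Make the other a sensitivity analysis and add a tipping-point check.
- Exempt primary and safety outcomes from the 50% removal rule, and report them with the amount missing.

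The cost is analysis wording and a little more programming; recruitment, visits and treatment are unchanged. If missing counts as not healed, healing rates fall and so does power: about 75% at 10% missing and 65% at 20%, against about 80% and 75% when cases are dropped, under the assumptions above. That rule is itself a single imputation, and in an open-label trial it could favour cell therapy if controls drop out more often. This is why the sensitivity analyses are part of the fix.

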### Adverse effects

Risks related to the use of autologous ASCs have not yet been described, considered non-existent for this study if they follow a rigorous cell production process. Treatment-related risks are those related to the surgical anesthetic procedure: surgical site infections, surgical wound dehiscence, worsening of pain in the treatment area, bleeding, gangrene, and cellulitis.

Partial data analysis will be conducted once at least five participants have been included in each group. The study will be halted if a statistically significant difference is observed in the primary or secondary safety outcomes for either group. In such a case, the Ethics and Research Committee/National Research Ethics Commission (CEP/CONEP) will be notified, and all necessary measures will be implemented.

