## Method

### Study design

This is a phase I/II, single-center, randomized clinical trial (RCT), PROBE (Prospective Randomized Open, Blinded Endpoint), controlled to evaluate the safety and efficacy of using ASCs to treat injuries in patients with PAD and advanced-stage CLI. The study was designed to attend the guidance Standard Protocol Items: Recommendations for Interventional Trials for clinical trial protocols (SPIRIT). (S1 File SPIRIT checklist)

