### Sample size and Statistics

The results obtained through the primary and secondary outcomes will be tabulated weekly in an electronic spreadsheet by the study monitoring team. A sample of 40 participants is estimated. The data will initially be evaluated using descriptive statistics, with median/variance and/or mean/standard deviation analyses for quantitative variables and contingency table analyses for categorical/qualitative variables. To effectively recruit the intended number of participants, our strategy involves having study team members to actively engage with patients in the outpatient clinics and wards of HC-FMB. This direct approach will ensure that we connect with a wide range of patients who meet the criteria to participate in the study, maximizing our chances of success.

All data monitored in the study for Group 1 (cell therapy) and Group 2 (control) will be statistically compared. Quantitative data will be evaluated for their distribution (using the Shapiro-Wilk normality test) and compared using the T-test or the Wilcoxon test, depending on the type of distribution of the variables. For categorical variables, differences will be evaluated using Pearson’s Chi-square test or Fisher’s exact test. Bonferroni coefficient and multivariate analysis will also be used. In all statistical tests, the significance level of the independent variable will be set at 5% (p < 0.05).

Finally, the evaluation of the entire data set using multiple correspondence analysis (MCA) is proposed. For its application, each quantitative variable will be categorized according to the distribution quartiles of their respective data.

Categorical variables will be evaluated by means of Fisher’s exact test, continuous variables will be compared with non-parametric methods such as the Mann-Whitney test or U test, pairwise comparisons will be evaluated with the Wilcoxon test, multivariate analyses will be evaluated with regression analysis Cox curves, long-term clinical analyzes will be compiled into Kaplan Meir curves.

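### The only scheduled trial-level safety comparison comes at five included per group, so nominally 15 of the 20 cell-therapy participants follow it with no later look stated

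*Protocol article*

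**What the plan says.** The trial-level rule stands in the protocol article under Adverse effects. It sets one analysis: "Partial data analysis will be conducted once at least five participants have been included in each group". The next sentence reads: "The study will be halted if a statistically significant difference is observed in the primary or secondary safety outcomes for either group". If that happens, the ethics committee and the national commission (CEP/CONEP) are to be notified.

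Other parts of the article touch on safety without adding a trial-level trigger:

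- **Sample size and Statistics:** primary and secondary outcomes "will be tabulated weekly in an electronic spreadsheet by the study monitoring team". No comparison or threshold is attached.
- **Data standards:** clinical monitors verify protocol adherence, data accuracy, and participants' rights and safety, and their reports are reviewed periodically. No criterion for pausing the trial is given.
- **The two Discontinuation criteria sections:** these rules act on individual participants (for example after major amputation, clinical worsening or ulcer infection), not on the trial.

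Study design labels the trial phase I/II, and Primary outcomes includes a safety outcome, absence of major amputation. Sample size gives 20 participants per group.

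**The concern.** The article does not leave safety monitoring to another document. It states a halting rule and gives one occasion on which it can operate, very early in the trial. Most exposure to the cell product comes afterwards. A harm that first shows itself among later participants would meet no scheduled comparison before the final analysis, although the data for one are compiled every week.

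This is a matter of how much of the trial the rule covers, and it is separate from the error rate of the first look. Even a perfect test at five per group would say nothing about harm accruing later.

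**Working it through.** **Inputs.** 20 per group, 1:1 (Sample size). Look at five or more included per group (Adverse effects). Fisher's exact test and a 5% level (Sample size and Statistics). Cell expansion of 14–21 days (Abstract, Methods). Visits to day 120 (Participant timeline). Recruitment from 1 June 2025 to 1 July 2027, 25 months (Recruitment). The event risks below are assumptions, because the article gives none for safety outcomes.

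**1. The plan's own figure.** For 75% v 30%, two-sided 5%, 80% power and pooled variance:

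n = [1.96 × √(2 × 0.525 × 0.475) + 0.8416 × √(0.75 × 0.25 + 0.30 × 0.70)]² / 0.45² = (1.384 + 0.531)² / 0.2025 ≈ 18.1, so 19 per group.

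The stated 20 is consistent with this, so 20 per group is used as the base.

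**2. Share of Group 1 after the look.** 20 − 5 = 15, and 15/20 = 75%. Two things move this figure:

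- The trigger is a minimum of five in *each* group, so Group 1 may already exceed five. If the 20 + 20 allocations fall in simple random order (an assumption), Group 1 stands at exactly five in about 64% of sequences and at 5.9 on average, leaving about 14.
- The trigger counts inclusion. Group 1 waits 14–21 days for cells, so some of those included may be untreated at the look. Counted by treatment, the number after it can exceed 15.

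**3. Calendar.** With even accrual (assumed), 40/25 = 1.6 per month. Ten participants are included at 10/1.6 ≈ 6 months, and about 19 months of recruitment follow.

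**4. What the 5 v 5 look can detect.** Two-sided Fisher p-values:

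| Events | Calculation | p |
|---|---|---|
| 3 v 0 | 2 × 10/120 | 0.17 |
| 4 v 1 | 2 × (25 + 1)/252 | 0.21 |
| 4 v 0 | 2 × 5/210 | 0.048 |
| 5 v 1 | 2 × 5/210 | 0.048 |
| 5 v 0 | 2 × 1/252 | 0.008 |

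Only the last three reach p<0.05. For an assumed 40% v 10%, the chance of one of them is 0.0768 × 0.5905 + 0.0102 × 0.5905 + 0.0102 × 0.3281 = 0.0453 + 0.0060 + 0.0034 ≈ 5.5%. For 50% v 10% it is 12.1%. Both figures are for one outcome and assume that it is already observed in all ten participants.

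**5. Harm not yet visible.** The chance of no event among the first five treated is (1 − p)⁵: 0.9⁵ = 0.59 at 10% and 0.8⁵ = 0.33 at 20%. In the next 15, the expected numbers of cases are 15 × 0.1 = 1.5 and 15 × 0.2 = 3.

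**6. Illustration of later looks.** One-sided exact tests for excess in Group 1 at 10 and 15 per group, by full enumeration, one outcome, outcomes treated as observed:

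| Assumed risks | Flagged, 0.025 per look | Flagged, 0.05 per look |
|---|---|---|
| 40% v 10% | 34.5% | 49.6% |
| 50% v 10% | 55.8% | 70.2% |
| 20% v 10% | 4.4% | 10.7% |
| 10% v 10% | 0.3% | 1.4% |
| 20% v 20% | 1.0% | 2.9% |
| 30% v 30% | 1.2% | 3.0% |

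**The case against.** **The halting sentence may be a standing rule.** It is not expressly confined to the partial analysis, and outcomes are tabulated weekly. That reading is open. But a significant difference can be observed only when a comparison is run, and none is scheduled after the first. If a standing rule was meant, the article should say so.

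**Other protection exists.** A reader might infer that nothing could stop the trial after the first look, whatever harm accrued. The article does not support that. Its monitors verify safety, individuals can be withdrawn for safety reasons, ethics and regulatory oversight continues, and the full protocol and monitoring plan, which are not shown, may add more. What stands is that none of this, as described, supplies a trial-level halting criterion or a later comparison.

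**Later looks may help less than the table suggests.** This stands in large part. A reader might infer that they would reliably catch modest harms, but 20% v 10% is flagged in only about 4% (11%) of trials. The higher figures depend on assumed risks of 40–50% v 10%. Follow-up matters too. At 0.8 per group per month, 10 and 15 per group are included at months 12.5 and 18.75. Adding 134–141 days (about 4.5 months) for expansion and follow-up puts complete data near months 17 and 23, when about 14 and 19 per group are already included. Looks on incomplete follow-up would come earlier but with less power.

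**The comparison with the first look is uneven.** This also stands. A two-sided test is set beside one-sided ones, and the stated look covers every primary and secondary safety outcome, so 5.5% is not its overall chance of halting. The false-flag rates are likewise per outcome and would rise if several were tested.

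**Conclusion.** The point holds as one of coverage. The article states a halting rule but schedules one occasion for it to operate, after which nominally 15 of 20 Group 1 participants are still to come (about 14 on average under simple random order, possibly more counted by treatment). That count follows from the article's own figures. The detection probabilities rest on assumed event risks and fully observed outcomes. They show that the single look is weak; they do not predict what later looks would achieve. In a phase I/II trial with safety among its primary outcomes, the gap is worth closing, but it does not mean that participants are left without any protection.

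**What to change.** Amend the Adverse effects section in two respects:

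1. State that the halting sentence applies throughout the trial.
2. State that the same statisticians repeat the safety comparison from the existing weekly tabulation at later points fixed in advance (for example at 10 and 15 treated per group). Say whether participants are counted by inclusion or treatment, and how much follow-up each look needs.

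The sponsor and CEP/CONEP should set the outcomes and the threshold before recruitment reaches those points. The illustration above shows what such looks might do and is not a recommended rule.

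The cost is one amended paragraph, two short tabulations by staff already in place, and a small chance of a false pause: in the illustration, at most about 1% (0.025 per look) or 3% (0.05 per look) per outcome when both groups share a risk of 10–30%. Looks that can act only on harm do not use up the efficacy significance level.

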### Primary outcomes

#### Safety.

Absence of major amputations (ankle, leg, or thigh).EfficacyTotal ulcer epithelialization and limb salvage rate (non-occurrence of a major amputation).

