### Secondary outcomes

#### 
Safety.

Death, acute myocardial infarction (AMI), cerebrovascular accident (CVA), thromboembolic events such as deep vein thrombosis (DVT) and pulmonary embolism (PE), systemic infectious condition, cancer, local infections, bleeding, worsening pain and enlargement of the ulcer area.Any adverse event not mentioned in the previous items or negative and clinically significant changes in laboratory parameters (glycemia, glycated hemoglobin, HDL, LDL, total cholesterol, triglycerides, leukogram, hematocrit, uric acid, urea, creatinine, CRP, sodium, potassium, alkaline phosphatase (ALP), alanine transaminase (ALT), aspartate transferase (AST), gamma-glutamyl transferase (GGT), bilirubin, total protein, albumin, prothrombin time (PT), partial thromboplastin time (PTT)) and tissue histological analysis.

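### The interim rule halts the trial on any significant difference in any of 35 to 37 safety outcomes at about five per group: it has little power for excess amputations, and its false-halt risk is left undetermined

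*Protocol article*

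**What the plan says.** Under Adverse effects, the Protocol article sets the timing: "Partial data analysis will be conducted once at least five participants have been included in each group". The consequence is mandatory: "The study will be halted if a statistically significant difference is observed in the primary or secondary safety outcomes for either group". The ethics bodies are then notified.

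The outcomes that can trigger the halt are listed elsewhere:

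- The primary safety outcome is "Absence of major amputations (ankle, leg, or thigh").
- The secondary list opens with "Death, acute myocardial infarction (AMI), cerebrovascular accident (CVA), thromboembolic events such as deep vein thrombosis (DVT) and pulmonary embolism (PE), systemic infectious condition, cancer" and goes on to local infection, bleeding, worsening pain and ulcer enlargement. That is 11 named events.
- It then adds any other adverse event, "negative and clinically significant changes in laboratory parameters" with 23 parameters named, and tissue histology.

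The level comes from Sample size and Statistics: "In all statistical tests, the significance level of the independent variable will be set at 5% (p < 0.05"). The same section says "Bonferroni coefficient and multivariate analysis will also be used", without saying which tests this covers. For categorical data it first allows Pearson's chi-square or Fisher's test and later names Fisher alone. For quantitative data it first allows the t-test or Wilcoxon and later names Mann-Whitney.

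**The concern.** A stopping rule should have a good chance of catching serious harm and a small, known chance of stopping a trial in which nothing is wrong. This one ties a mandatory halt to statistical significance in any item of a long, mixed list, in either direction, with about ten participants in hand. Rare binary events can hardly reach p<0.05 at that size, whereas many laboratory comparisons give many chances of a spurious result.

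The trigger is inclusion, not completed follow-up. The Abstract gives 14 to 21 days for cell expansion, and Participant timeline gives 120 days of follow-up. The most recently included Group 1 participants may not have received cells when the look falls due.

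At stake are a 40-patient trial that could end at about ten for no reason, and a formal safety check that would usually miss a real excess of limb loss.

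**Working it through.** **Stated figure.** The article gives no operating characteristic for the interim rule. Its only related figure is 20 per group for healing rates of 75% v 30%, 80% power, two-sided 5%. With mean proportion 0.525, n = [1.96√(2×0.525×0.475) + 0.8416√(0.75×0.25 + 0.30×0.70)]² / 0.45² = (1.384 + 0.531)² / 0.2025 ≈ 18.1, so 19 per group. The planned 20 is consistent with this, and it is not in dispute here.

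**Number of outcomes.** 1 primary + 11 named events + 23 laboratory parameters = 35. Any other adverse event and histology make 37.

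**Detecting excess amputations at 5 v 5.** Enumerating all tables:

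- Fisher, two-sided: 3 v 0 gives p=0.167. Only 4 v 0 (0.048), 5 v 0 (0.008) and 5 v 1 (0.048) fall below 0.05.
- Uncorrected chi-square: 3 v 0 gives p=0.038 and 5 v 2 gives 0.038, so both halt, as do the three tables above.

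The article states no amputation risks, so those below are assumptions. Worked case for Fisher, 40% v 10%: P(4 v 0) = 0.0768×0.5905 = 0.0453; P(5 v 0 or 5 v 1) = 0.01024×(0.5905+0.3281) = 0.0094; total 0.0548.

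| Assumed risks | Fisher | Chi-square |
|---|---|---|
| 20% v 10% | 0.4% | 3% |
| 30% v 10% | 1.9% | 10% |
| 40% v 10% | 5.5% | 19% |
| 60% v 10% | 22% | 43% |

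These figures assume that every participant's outcome is known at the look. Incomplete follow-up lowers them.

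**False halt, reading A: 23 laboratory values compared as continuous variables at an unadjusted 5%.** If independent, the t-test gives 1 − 0.95²³ = 69%. Exact Mann-Whitney at 5 v 5 has attained size 8/252 = 3.17%, so 1 − 0.9683²³ = 52%. Simulation of equally correlated normal values with no true difference gives:

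| Correlation | t-test | Mann-Whitney |
|---|---|---|
| 0 | 69% | 52% |
| 0.3 | 59–61% | 45–46% |
| 0.5 | 49–50% | 37% |
| 0.7 | 35% | 26–27% |

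The spans reflect simulation error between runs.

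**Reading B: all 37 outcomes are yes/no events.** With independent outcomes at a common rate, the risk is 1 − (1 − s)³⁷, where s is the test's actual size at 5 v 5. For Fisher, s is 0.00005, 0.00055, 0.0047 and 0.0121 at event rates of 5%, 10%, 20% and 30%. The risk is then 0.2%, 2%, 16% and 36%. Uncorrected chi-square would give 6%, 31%, 76% and 89%, although at five per group it is a poor approximation.

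**Reading C: Bonferroni over all outcomes.** The threshold is 0.05/37 = 0.00135 (0.05/35 = 0.00143 without the two open items). The smallest two-sided p at 5 v 5 is 2/252 = 0.0079 for both Fisher and exact Mann-Whitney, so neither can halt the trial. Even 5 v 0 amputations gives 0.0079 with Fisher and 0.0016 with uncorrected chi-square. Only a t-test on a quantitative variable could still cross the threshold.

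**The case against.** The strongest counter-argument concerns false halts. A reader might infer from the length of the outcome list that the trial will probably stop by chance. The article does not support that as a general statement. Its wording for the laboratory outcome fits a yes/no event in the harm direction, and Fisher's test on such events stays below even odds at every rate examined. On the continuous reading, Mann-Whitney exceeds one half only if the values are nearly independent. That is implausible for a panel holding total cholesterol with LDL, urea with creatinine, and ALT with AST. Bonferroni is also named, and could remove false halts almost entirely. This objection stands, and the risk has to be given by reading.

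A second inference is that the rule is an efficacy look that spends type I error, because amputation also appears as limb salvage among the primary efficacy outcomes. This is minor. The article describes a safety halt and allows no efficacy claim from it. Under Fisher at 5 v 5 with equal risks, the chance of an amputation signal in either direction is about 0.5% at a risk of 20%, 1.2% at 30% and 2.1% at 50%. The sample size rests on healing.

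Third, five per group is a minimum. This helps little: at ten per group Fisher still gives only 5.7% for 30% v 10% and 15% for 40% v 10%.

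Fourth, outcomes are tabulated weekly and clinical monitors check participants' safety, so this look is not the only safeguard. That is true, but it does not repair the one formal halting rule described.

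Fifth, an unseen analysis plan may settle the test and the threshold. It may, but the article itself fixes a mandatory halt, its outcome list and its timing, and each of the readings available gives a poor rule.

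**Conclusion.** The point holds. As written, the rule covers 35 to 37 outcomes in either direction, at a look triggered by inclusion, and each reading leaves it prone to false halts, nearly inert for serious harm, or both.

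The firmest part is low power for excess amputations: 5.5% with Fisher and 19% with uncorrected chi-square at 40% v 10%. This rests on assumed risks, exactly five per group and complete outcomes. Whether 3 v 0 halts depends on which permitted test is used.

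The false-halt risk has no single value. It is about 26 to 69% on reading A (correlation 0 to 0.7), 0.2 to 36% on reading B with Fisher, and zero with exact tests on reading C. A claim that a chance halt is more likely than not would need particular conditions, such as weakly correlated laboratory values tested at an unadjusted 5%, or chi-square on frequent yes/no events. The article does not establish these.

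**What to change.** Amend the Adverse effects section so that:

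- the formal rule applies only to a short list of serious outcomes, named by the sponsor and its safety reviewers, and only in the harm direction;
- statistical significance is replaced by a boundary whose false-halt and detection probabilities at the interim sample size are stated. The sponsor and its safety reviewers choose the method and the threshold; a posterior-probability boundary is one option among several;
- laboratory and other adverse-event comparisons at this look are descriptive but still reviewed;
- the look is triggered by a stated length of follow-up in a stated number of participants;
- the text says that there is no stopping for benefit.

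The cost is amendment wording and a small table of operating characteristics. Waiting for follow-up makes the formal look later. The main downside is that a laboratory difference no longer halts the trial automatically.
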